### Study intervention and implementation

The package of powdered products will be either a placebo powder. The barberry or placebo powders will be packaged in undetectable non-transparent wrappers. Placebo powder contains 9 g maltodextrin, 1 g citric acid, 1 g milled sucrose, and edible red color, and the barberry powder contains 10 g milled dried barberry and 1 g of milled sucrose. All dried barberry is purchased from the local market. Each patient receives 60 packages, each containing barberry or placebo powder for daily use. The daily amount of 10 g of barberry powder was selected based on a previous study by Shidfar et al. in which the amount of extract obtained from 10 g of barberry powder was investigated [22]. The time of consumption of powders can be during any time of the day and participants will not be imposed to take the supplements at a specific time of the day. Since a change in dietary habits or physical activity can affect the outcome of the study, participants will be asked not to change their daily diet and to continue their daily physical activity. Furthermore, patients will be instructed to maintain their current type/dose of oral medication during this trial period.

### Compliance

All participants will be called biweekly to assess their compliance. Participants will be asked to mark a reminder note for the daily consumption of the packages. They will be given a sheet of paper that includes the code, the next visit date, two columns entitled “one package daily” and another column entitled “Date” to record their regular consumption of package. Patients are asked to bring empty packages to the hospital at the end of the study period.

### Outcome measurements

#### Dietary assessment

Before and after the 8-week intervention, a 3-day 24-h dietary recall questionnaire will be obtained to evaluate the usual dietary intake. It includes two workdays and one weekend. Then, the obtained data from the questionnaire will be assessed using N4 software (NUTRITIONIST 4, First Data Bank, San Bruno, CA, USA).

#### Anthropometry measures

The height will be measured without shoes by a stadiometer (Seca, Germany) with a sensitivity of 0.1 cm and weight with a digital scale (808 Seca, Germany) while wearing light clothes (with no coat or raincoat) with a sensitivity of 0.1 kg before and after of 8-week intervention. Body mass index (BMI) will be calculated by dividing the weight (in kilograms) by height squared (in meters).

#### Blood pressure

Before and after of 8-week intervention, 24-h ABPM with an automatic monitor in oscillatory mode will be performed in the electrophysiology department of the hospital. The change in blood pressure during the 24-h period is recorded by this device. The blood pressure cuff is placed and fixed around the upper left arm. The digital blood pressure monitoring machine itself is attached to a belt around the waist or hangs on the neck. Technician checks that battery life is sufficient for 24 h and checks if the machine operates well. The cuff inflates every 30 min in the day and every 1 h in night time as per the settings and then slowly deflates to record the blood pressure in its memory. Patients will be asked to have their usual lifestyle and activities at this 24-h ambulatory blood pressure monitoring.

#### Laboratory investigations

##### Blood sampling

A 10-mL venous blood sample will be taken in a 12-h fasting state between 8:30 and 10:00 a.m. by the hospital lab technician and stored in a heparinized tube. Plasma separation will then be performed by centrifugation at a speed of 1000*g* for 15 min. Then, the plasma will be collected into separate micro-tubes and will be stored in a freezer at − 80 °C until laboratory analysis.

##### Blood chemistry

TG, TC, HDL-C, and LDL-C concentrations will be measured by auto-analyzer Selectra ProXL (Vital Scientific, Spankeren, The Netherlands) using commercially available kits through enzymatic colorimetric methods as per the manufacturer’s instructions. Plasma CRP will be measured using a turbidometric immunoassay kit by an auto-analyzer. Plasma IL-6 will be measured using a commercially available ELISA kit (BioLegend, USA).

##### Urinary test

Twenty-four-hour urine will be collected to measure its volume, creatinine, sodium, and nitrite/nitrate-concentrations. Urinary sodium will be measured by flame photometry to estimate sodium intake. Urine nitrite/nitrate concentrations will be determined using a colorimetric assay (Cayman Inc., USA). At baseline and the end of the study, patients are given a 24-h urine container to be filled by collected urine of the patient. The 24-h urine collection will be performed concurrently with 24-h blood pressure monitoring and the patient will return the container to the hospital the next day. The volume of collected urine will be recorded and a sample will be aliquoted into the micro-tubes to be stored in the freezer at − 80 °C until further measurements.

### Atherosclerotic cardiovascular disease risk score

Ten-year risk of atherosclerotic cardiovascular disease [26] will be determined at baseline and after the intervention.

#### Safety procedures

We will record and report all adverse events. Participants with abnormal research samples will be referred to a specialist.

#### Data management and monitoring

Participants will be given a code number between 1 and 80. The master randomization list will be safely stored. Interim analyses will not be performed. When the intervention period is finished, the collected data will be entered in the SPSS software (SPSS Inc., Chicago, IL, USA).

The trial will be monitored by internal monitoring. The study leader provides monitoring of overall trial progress. During the study, regular meetings of the principal investigator and study leader will be held to discuss concerns and review the progress. Any information that is available on serious adverse events believed to be due to treatment will be supplied to the study cardiologist. If there will be suspicion of harm, discontinuation of the trial will be reviewed.

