### Randomization/blinding

Participants will be randomized to receive either the barberry or the placebo product. The randomization will be performed with the aid of a sequence generated by using a random number table. For this purpose, each row of the table was considered as a block, and from the left, in the order in the table, odd numbers were considered as group A and even numbers were considered as group B. If the first two allocations were for one of the A or B, the next two allocations were considered for the second group. The sequence of each block was placed in a sealed opaque envelope. Diabetes and hyperlipidemia are two other major CVD risk factors that may coexist with hypertension. To achieve a balanced distribution of these risk factors in each of the study groups, stratified block randomization will be performed, with four strata: with a history of diabetes, without a history of diabetes, receiving statins, and not receiving statins. A block size of 4 within each stratum will be used, with a 1:1 randomization between the two groups.

This trial has a single-blinded manner. Patients are blinded to the type of product they are consuming, but the main investigator who assigns patients to intervention or placebo groups is not blinded. Placebo and barberry powdered products are given to patients in undetectable non-transparent packaging.

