### Ancillary and post-trial care

In these patients, if no specific side effects are observed, if desired, the barberry powder for regular use will be recommended to patients.

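### Serious adverse events are sent to the study cardiologist on condition that they are already believed to be due to treatment, and the one stated analysis set leaves out participants who drop out for side effects

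*Protocol article*

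**What the plan says.** Five parts of the protocol article bear on this.

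- **Safety procedures** makes a general commitment, with no recipient named: "We will record and report all adverse events".
- **Data management and monitoring** sets the route to the cardiologist: "Any information that is available on serious adverse events believed to be due to treatment will be supplied to the study cardiologist". The same section says "The trial will be monitored by internal monitoring", that "regular meetings of the principal investigator and study leader will be held to discuss concerns and review the progress", that "Interim analyses will not be performed", and "If there will be suspicion of harm, discontinuation of the trial will be reviewed".
- **Randomization/blinding** says that patients are blinded but that "the main investigator who assigns patients to intervention or placebo groups is not blinded".
- **Eligibility** lists any side effect among the drop-out criteria. **Statistical analyses** describes one analysis set, per-protocol, limited to participants who complete the study.
- **Ancillary and post-trial care** allows barberry to be recommended for regular use after the trial "if no specific side effects are observed".

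**The concern.** Relatedness is normally something a medical reviewer assesses after seeing an event. Here it is a condition for the event being sent to that reviewer. Everyone in this trial is already on antihypertensive medication, and the product is being tested for an added blood-pressure effect. A serious event to which the product contributed could reasonably be put down to background drugs or underlying disease. The study cardiologist is well placed to question that attribution, yet the protocol does not require such an event to be put before them.

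The usual protection against mistaken attribution of single cases is to look at all events by arm. No interim comparison is planned, so that look comes at the end at the earliest. If it were then made in the completers set, participants who left because of side effects would be missing from it. What is at stake is how complete the safety picture is, both during the trial and in the report. The primary systolic blood pressure comparison does not depend on the escalation rule.

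**Working it through.** The documents give no adverse event rate and no figure for how often causality is misjudged, so there is no plan figure to reproduce. The check is a comparison of the sections.

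**Step 1: what each safety sentence covers.**

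| Section | Events covered | Recipient | Condition on cause |
|---|---|---|---|
| Safety procedures | All adverse events | Not named | None |
| Data management and monitoring, cardiologist sentence | Serious adverse events | Study cardiologist | Believed due to treatment |
| Data management and monitoring, meetings | Concerns and progress | Principal investigator and study leader | None |
| Data management and monitoring, harm sentence | Suspicion of harm | Not named | None stated |

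The first two rows can both be obeyed in full. They differ in scope, and the article does not say how they fit together.

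**Step 2: trace a serious event judged unrelated.** It is recorded and reported under Safety procedures, to a recipient not named. The cardiologist sentence does not apply to it. It may be raised at the meetings, but these are not described as reviewing every serious event. No sentence takes it to the cardiologist.

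**Step 3: who forms the belief.** The article does not say. Patients are the only people described as blinded, and the main investigator is expressly not blinded. The blinding status of the cardiologist is not stated.

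**Step 4: could a pattern across events show up another way during the trial?** Not through a planned comparison, because interim analyses are excluded and data are entered into SPSS only once the intervention period is over.

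**Step 5: the end-of-trial comparison.** Any side effect may lead to drop-out (Eligibility), and analysis is restricted to completers (Statistical analyses). A participant who drops out for a side effect is therefore outside the analysed set.

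The scale of possible drop-out can be read from the Sample size section. The requirement is 66 and the recruitment target is 80, which leaves 80 − 66 = 14. The stated allowance of about 20% gives 0.20 × 80 = 16. The plan thus allows for some 14 to 16 participants outside the completers set. How many would leave because of side effects is unknown.

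**The case against.** The strongest reply is that the cardiologist sentence sets a minimum duty. It does not say that other serious events are withheld, and the word only does not appear. That is correct. A reader might infer a prohibition, but the text supports only the weaker statement that no route is given for those events.

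Four further inferences are tempting and should not be drawn.

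- *That the sentence contradicts the promise to report all adverse events.* It does not. Recording and reporting everything is compatible with escalating a subset to one person.
- *That the cardiologist is the sole gateway to any review of harm.* The meetings and the suspicion-of-harm sentence carry no causality condition, and the Auditing section provides for audits during and after the study.
- *That the unblinded main investigator judges causality.* No section says so. The text does not exclude it and names no one else, which is a reason to specify the point but not evidence of bias.
- *That the final safety data or the post-trial recommendation rest on filtered events.* The sentence governs escalation during the trial, not what is recorded. The post-trial condition refers to side effects observed, not to those that reached the cardiologist.

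It can also be said that a journal article leaves safety procedures to the full protocol. That covers the silence on who judges cause. It does not cover the condition itself, which is written into the article as the rule to follow. On the tabulation, it is fair to say that this is usually analysis-plan content and that all events are already promised in the report. But the article states one analysis set, completers, with no exception for safety, and pairs it with a drop-out criterion based on side effects. That combination is stated, not omitted.

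**Conclusion.** The concern holds in a limited form. As written, serious events judged unrelated to treatment need not reach the study cardiologist, in a trial with an unblinded main investigator, internal monitoring and no interim comparison. In addition, a safety comparison made in the stated analysis set would omit participants who dropped out for side effects.

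The size cannot be given. A reader might want a probability that events are missed, but with no event rate and no misattribution rate in the documents any such figure would only restate its own assumptions. The first part rests on reading the cardiologist sentence as the working rule, with no wider rule elsewhere. The second rests on the per-protocol statement applying to safety as well as efficacy, which the article neither says nor excludes. This is a weakness in safety oversight that should be corrected. It does not show that events will be hidden or that the safety comparison is biased.

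**What to change.** 1. Reconcile Safety procedures with Data management and monitoring so that every serious adverse event is supplied to the study cardiologist whatever its believed cause, identified by participant code and without the arm.
2. Record relatedness as a data field, not as a condition for reporting, and state who assesses it and whether that person knows the arm.
3. State that all adverse and serious adverse events will be tabulated by arm in all randomised participants, not only completers, regardless of attribution.

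The cost is a few sentences of protocol text and some additional case summaries for a cardiologist already attached to the study, in a trial of 80 participants followed for 8 weeks. The small downside is that the cardiologist will review some events that are clearly unrelated. No change to treatment, to the drop-out criteria or to the review of discontinuation is proposed.

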### Protocol amendments

During the study, any changes and amendments will be reviewed by the principal investigator and should be agreed to by the other study investigators. If approved, the amendments will be recorded with a justification and will eventually be reported.

#### Statistical analyses

Data analysis will be done using SPSS version-21 software. A per-protocol analysis will be carried out, in which only participants who complete the full study protocol will be included. All results will be assessed for normality, and skewed distributions will be log-transformed before analysis. To describe the quantitative data, the mean and standard deviations will be used, and to describe the qualitative data, frequency and percent will be used. Between-group differences will be tested by independent sample *t* test and Mann-Whitney *U* test as the parametric and nonparametric tests respectively. Paired-sample *t* test and nonparametric Wilcoxon signed ranks test will be used for evaluating within-group differences in normally and non-normally distributed data, respectively. Chi-square or Fisher exact tests will be used for qualitative variables. Parametric or nonparametric analysis of covariance (ANCOVA) will be used for adjusting baseline levels for comparing between groups results. In this study, *P* value less than 0.05 will be considered statistically significant.

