### Primary objective

To evaluate the effect of 8-week barberry consumption on variations in SBP measures in patients with hypertension and other cardiovascular risk factors.

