### Eligibility

The inclusion criteria for subjects include (1) willingness to participate in the study, (2) age between 20 and 65 years, (3) known hypertensive patients on medical treatment, and (4) at least one other classical CVD risk factors, including hyperlipidemia, diabetes mellitus, or smoking. Exclusion criteria include (1) unwillingness to continue participation, (2) having BMI > 30, (3) patients on nitrate drugs, (4) taking high doses of statins (Atorvastatin> 40 mg/day or Rosuvastatin> 20 mg/day), (5) consumption of vitamins or minerals supplements during the past month, and (6) having chronic kidney disease stage 4 or 5. The drop out criteria include any side effects, refusing to continue the study, missing telephone responses, and any restrictive illness. Participants are allowed to withdraw from the study at any time.

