### Sample size

Sample size calculations were carried out using G*Power V.3.1.9.2 software [25]. The sample size was calculated based on data from Tjelle et al. [15], a relatively similar polyphenol-rich berry juice intervention study that observed a reduction in SBP of 6.2 mmHg compared to placebo. Assuming equal standard deviation in both group and by considering pooled value of the standard deviation = 8.8, a significance level of *α* ≤ 0.05 and statistical power of 80%, the minimum sample size will be 66 patients will be required to detect a change of this size in the SBP level. To account for a drop-out rate of approximately 20%, we plan to recruit 80 participants (40 randomized to each group).

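### The only stated analysis of a superiority question on SBP is per-protocol in completers, which exposes the comparison to selection after randomisation

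*Protocol article*

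**What the plan says.** The question is one of superiority. The Primary objective is "To evaluate the effect of 8-week barberry consumption on variations in SBP measures", and the Hypotheses section expects blood pressure to improve with barberry. The Statistical analyses section names a single analysis set: "A per-protocol analysis will be carried out, in which only participants who complete the full study protocol will be included". The document contains no intention-to-treat analysis, no missing-data method and no sensitivity analysis in all randomised participants.

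The Eligibility section defines who leaves: "The drop out criteria include any side effects, refusing to continue the study, missing telephone responses, and any restrictive illness". The Sample size section allows for about 20% loss and randomises 80, 40 per group. ABPM is performed before and after the 8 weeks (Blood pressure section), and after the packages are handed out the next visit is the final one (Setting section). For between-group comparisons the plan offers t or Mann-Whitney tests, and ANCOVA to adjust for baseline.

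**The concern.** Randomisation makes the two arms comparable when they are formed. An analysis confined to completers compares subsets chosen by what happened afterwards. Here the exits include any side effect, and the two powders differ in composition (milled dried barberry against maltodextrin with citric acid), so tolerability may differ by arm. Read literally, a side effect or a run of missed calls can also exclude someone whose week-8 blood pressure could still be measured.

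If those lost from the barberry arm would have had poorer SBP changes than those who stay, and the placebo losses do not mirror this, completers will show a benefit that the product did not cause. Adjusting for baseline SBP does not help, because the selection concerns tolerability or response during follow-up and not the starting level. At stake are the size of the SBP estimate and the validity of its 5% significance level. The plan has no all-randomised result against which a reader could check the completer result.

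**Working it through.** **Inputs.** From the Sample size section: difference 6.2 mmHg ("observed a reduction in SBP of 6.2 mmHg compared to placebo"), SD 8.8 ("considering pooled value of the standard deviation = 8.8"), power 80%, about 20% drop-out, 40 randomised per arm. From Statistical analyses: α = 0.05 ("value less than 0.05 will be considered statistically significant"). The protocol does not state sidedness; two-sided is assumed because it reproduces the stated total. The drop-out pattern by arm and the outcome gap between those lost and those who stay are assumptions; the documents give neither.

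**The plan's own figure.** For a two-sided t test with 33 per arm, the non-centrality is 6.2 / (8.8 × √(2/33)) = 2.86 and the power is 80.5%; with 32 per arm it is 79.2%. So 33 per arm, 66 in total, reproduces the stated minimum ("the minimum sample size will be 66 patients will be required to detect a change of this size in the SBP level"). The point does not rest on an error in that number.

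**Bias in completers when the true effect is zero.** Let p be the fraction lost in an arm and g the amount by which those lost would have been worse than completers. If the arm's overall mean change is 0 and the completers' mean is m, then (1 − p)·m + p·(m + g) = 0, so m = −p·g. The spurious benefit of barberry is p_B·g_B − p_P·g_P.

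- Equal loss with the same gap in both arms: the terms cancel and the bias is 0.
- 20% lost in each arm, with only the barberry losses selective (g_P = 0). The gap is taken as 0.5 to 1 SD, that is 4.4 to 8.8 mmHg, and 32 v 32 are analysed:

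| Gap g_B | Bias = 0.20 × g_B | Share of 6.2 | Non-centrality = bias / (8.8 × √(2/32)) | Type I error |
|---|---|---|---|---|
| 4.4 | 0.88 mmHg | 14% | 0.40 | 6.8% |
| 8.8 | 1.76 mmHg | 28% | 0.80 | 12.4% |

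- Unequal loss with the same gap in both arms, 30% v 10% (28 v 36 analysed): a gap of 5 gives (0.30 − 0.10) × 5 = 1.0 mmHg and type I error 7.3%; a gap of 8.8 gives 1.76 mmHg and 12.2%.
- Milder imbalance, 20% v 10% with a gap of 2 in both arms: 0.2 mmHg and 5.1%.

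**Would imputation alone remove it?** Someone without a week-8 ABPM has no SBP reading after baseline. Imputing from arm and baseline variables gives such a person roughly the value of a similar completer in the same arm. With p = 0.20 and g = 4.4, completers average −0.88 and those lost would average −0.88 + 4.4 = 3.52. If baseline does not predict the gap, imputation fills in about −0.88, so the arm mean stays at −0.88. Adding a shift of 4.4 to the imputed values gives 0.8 × (−0.88) + 0.2 × 3.52 = 0. Removing the bias therefore needs observed week-8 values; a delta shift shows how much it could matter where values cannot be obtained.

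**Power when everyone is analysed.** Assume 40 per arm, SD 8.8, week-8 SBP available for all, and the 20% who drop out keeping a fraction f of the effect. The difference becomes 6.2 × (1 − 0.2 × (1 − f)).

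| f | Difference | Power, 40 v 40 | Total N for 80% |
|---|---|---|---|
| 1 | 6.20 | 87.5% | 66 |
| 0.5 | 5.58 | about 80% | 82 |
| 0 | 4.96 | about 70% | 102 |

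For comparison, 32 completers per arm with the full 6.2 mmHg have 79.2% power.

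**The case against.** The strongest reply is that the bias is conditional. If drop-out is similar in the two arms and bears the same relation to outcome, the completer comparison is unbiased, and nothing in the documents shows that it will be otherwise. The assumed gap of 0.5 to 1 SD has no source in the protocol. All of this stands. A reader might infer that the randomised comparison is certainly lost or the type I error certainly inflated; the documents support only a risk.

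Two further inferences are tempting and also go too far. One is that participants would leave because they see no benefit: patients are blinded, and the protocol describes no blood pressure visit between baseline and the end. The other is that the unblinded main investigator would steer who is counted as a drop-out: the Randomization/blinding section says that this person assigns patients, not that this person decides who has dropped out. The point rests on the listed drop-out criteria, above all side effects, and needs neither inference.

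It can also be said that a separate analysis plan may exist and may add an all-randomised analysis. That does not dispose of the matter. The protocol does not leave the analysis set open; it names one, and a later plan that made all randomised participants primary would contradict the sentence.

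Finally, the change is not free: follow-up of people who stop takes effort, and power may fall. That is correct and is counted under the fix.

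**Conclusion.** The point holds as a risk built into a stated choice. For a superiority comparison of SBP, the only analysis that the protocol specifies excludes people for events after randomisation that may depend on the product, with about 20% loss expected, and baseline-adjusted ANCOVA does not correct for that.

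In the hypothetical case with no true effect, 20% lost per arm, only the barberry losses selective and a gap of 4.4 to 8.8 mmHg, the spurious benefit is 0.9 to 1.8 mmHg (14% to 28% of the 6.2 mmHg target). The two-sided type I error is about 6.8% to 12.4% instead of 5%. These figures rest on the assumed gap and drop-out pattern, and with symmetric drop-out they fall to zero bias and 5%. Because the sole stated analysis of the primary outcome is affected, the sentence should be corrected before the data are analysed.

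**What to change.** Replace the per-protocol sentence in Statistical analyses with text to this effect:

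- The primary analysis includes all randomised participants in their assigned arm, regardless of compliance or product discontinuation.
- The week-8 ABPM that is already planned is sought from everyone, including those who stopped the product or missed calls, unless they withdraw consent.
- Remaining missing week-8 SBP is handled by baseline-adjusted ANCOVA or multiple imputation under missing-at-random.
- A delta-adjusted sensitivity analysis lets drop-outs be worse than that assumption implies, with the shift varied by arm.
- The per-protocol analysis is kept as supportive.

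The Eligibility wording on drop-out should be aligned, so that leaving the product does not by itself mean leaving follow-up for measurement.

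The cost is some follow-up effort, extra analysis work and a possibly smaller estimated effect. With 80 analysed, power is 87.5% if the full 6.2 mmHg holds in everyone, about 80% if the 20% who drop out keep half of it, and about 70% if they keep none; in that last case 80% power would need 102 participants. The Protocol amendments section provides a route, and Trial status dates this version 26 March 2020, within the 5-month recruitment period anticipated from 20 January 2020.

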### Secondary objectives

To compare within- and between-group variations in DBP, MAP, plasma lipid profile including total cholesterol (TC), low-density lipoprotein cholesterol (LDL-C), high-density lipoprotein cholesterol (HDL-C), triglyceride (TG), inflammatory biomarkers including plasma CRP and interleukin-6, and 24-h urinary NOx in patients with hypertension and other cardiovascular risk factors.

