### Hypotheses

Daily consumption of barberry will improve SBP, DBP, and MAP in patients with hypertension and other cardiovascular risk factors.

Plasma levels of lipids, CRP, and IL-6 will be reduced by daily consumption of barberry in patients with hypertension and other cardiovascular risk factors.

Urinary NOx will be increased by daily consumption of barberry in patients with hypertension and other cardiovascular risk factors.

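### Within-group change is a secondary objective tested at the same 0.05 level as the between-group comparison, and the plan does not say that only the latter decides efficacy

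*Protocol article*

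**What the plan says.** The Secondary objectives section of the protocol article begins "To compare within- and between-group variations in DBP, MAP, plasma lipid profile" and goes on to the individual lipids, CRP, IL-6 and 24-h urinary NOx. That makes nine outcomes: DBP, MAP, TC, LDL-C, HDL-C, TG, CRP, IL-6 and NOx.

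The Statistical analyses section gives the within-group part its own tests, the paired-sample t test or its rank counterpart: "nonparametric Wilcoxon signed ranks test will be used for evaluating within-group differences in normally and non-normally distributed data, respectively". It does not limit them to secondary outcomes. One threshold covers every test: a P "value less than 0.05 will be considered statistically significant".

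The same section also plans the randomised comparison. "Between-group differences will be tested by independent sample" t test or the Mann-Whitney test, and parametric or nonparametric ANCOVA "will be used for adjusting baseline levels for comparing between groups results". It does not say which of these results decides whether barberry works, or that the within-group results are descriptive.

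The Primary objective does not mention within-group change: "To evaluate the effect of 8-week barberry consumption on variations in SBP measures in patients with hypertension and other cardiovascular risk factors". The Sample size section is built on a 6.2 mmHg difference in SBP against placebo.

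**The concern.** The change within one arm mixes any barberry effect with whatever moves both arms over eight weeks: placebo response, regression to the mean, and altered behaviour or drug adherence under observation. Only the contrast between the randomised arms removes these. A paired test in the barberry arm therefore cannot answer the question for which the trial was designed.

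The familiar trap is the pattern in which the barberry arm changes significantly and the placebo arm does not. It looks like a treatment effect but is not a test of the difference between arms. Because within-group comparison is a stated objective with its own tests and the common threshold, an author who follows the plan could report such a pattern as meeting a secondary objective, even when the between-group comparison shows nothing.

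**Working it through.** **Inputs.** From Sample size: difference 6.2 mmHg, pooled SD 8.8, alpha 0.05, power 80%, minimum 66 patients, 80 to be recruited (40 per arm). That section does not say whether 8.8 is the SD of SBP or of its change. It is taken here as the SD of change, which is an assumption. The change common to both arms is also an assumption, because the protocol gives no expected placebo-arm change.

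**Step 1: the plan's own figure.** The normal approximation gives n per arm = 2 × (1.96 + 0.842)² × (8.8/6.2)² ≈ 31.6, so 32 per arm. The two-sample t calculation (noncentral t) gives 32.6, so 33 per arm and 66 in total, which matches the protocol. A one-sided test would need only 50 in total by the normal approximation, so the stated size is two-sided. The size thus refers to the between-group comparison.

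**Step 2: chance that one paired test shows a significant fall.** Let both arms have the same true mean fall δ, so that there is no barberry effect. With n = 33, the standard error of the mean change is 8.8/√33 = 1.532 mmHg and the noncentrality is δ/1.532. Then p is the probability that a noncentral t on 32 degrees of freedom exceeds the two-sided 5% critical value of about 2.04.

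**Step 3: chance of the barberry-only pattern.** The arms are independent, so P(significant fall in barberry, not in placebo) = p(1 − p).

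| Common fall δ (mmHg) | p, each arm | Barberry only, p(1 − p) |
|---|---|---|
| 0 | 0.025 | 2.4% |
| 1 | 0.092 | 8.4% |
| 2 | 0.244 | 18.4% |
| 3 | 0.476 | 24.9% |
| 4 | 0.716 | 20.3% |
| 5 | 0.886 | 10.1% |
| 6 | 0.967 | 3.2% |

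For example, at 3 mmHg: 0.476 × 0.524 = 0.249. The product cannot exceed 25%, which it reaches at p = 0.5.

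**Step 4: the between-group test on the same data.** In simulations of 50,000 trials per setting with 33 per arm, the two-sample t test on change wrongly favoured barberry in 2.3% to 2.5% of trials at common falls of 0, 2, 3 and 4 mmHg (about 5% two-sided). At 3 mmHg the barberry-only pattern appeared in 25.2% of trials. In 22.7% it appeared while the between-group test did not significantly favour barberry.

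**Step 5: sensitivity.** With 40 per arm the barberry-only rates are 20.5%, 24.7% and 16.0% for common falls of 2, 3 and 4 mmHg. With 33 per arm, the rates for the same three falls are 24.8%, 16.3% and 3.8% if the SD of change is 6, and 12.8%, 20.4% and 24.8% if it is 12.

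All rates are per outcome. The figures use the SBP planning SD. For another outcome, what matters is the common change relative to that outcome's own SD of change.

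**The case against.** The strongest reply is that the plan contains the right analysis. Between-group tests are listed first, baseline-adjusted ANCOVA is added, the sample size rests on a difference from placebo, and no sentence bases efficacy on the paired tests. This stands. It limits the point to the status and shared threshold of the within-group tests. A reader might infer that the trial would judge barberry by before-after change, or that the primary SBP objective is a within-group one. The protocol says neither.

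A reader might also take the Hypotheses section as a before-after claim ("Daily consumption of barberry will improve SBP, DBP, and MAP in patients with hypertension and other cardiovascular risk factors"). The sentence mentions no baseline and no change over time. In a placebo-controlled design it reads equally well as an ordinary statement of treatment effect, so it does not support the point.

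Next, 3 mmHg lies almost exactly where p(1 − p) peaks, so quoting 25% alone would mislead. That stands too, and the full range has to be shown. Several design features also work against a large common shift. Entry requires treated hypertension but no blood pressure threshold, baseline follows a two-week run-in, pressure is a 24-hour ambulatory record, and medication is to be held constant. On the other side, participants are telephoned every two weeks about compliance, so a modest shift in both arms remains plausible.

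Finally, replacing a paired P value by a per-arm 95% confidence interval changes little on its own, because the interval excludes zero exactly when the paired t test gives P < 0.05. This is correct. The statement of which result decides efficacy does the work.

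The reply that a condensed article may leave ranking of tests to a fuller document does not remove the point. The within-group objective, its tests and its threshold are written here.

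**Conclusion.** The point holds in a limited form and should be corrected. A secondary objective calls for within-group comparison. The analysis section tests it at the same 0.05 level as the randomised comparison and does not reserve efficacy conclusions for the latter.

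Under no true difference, with 33 per arm and 8.8 read as the SD of change, the misleading barberry-only pattern has a chance per outcome between about 2% (no common change) and about 25% (a common fall near 3 mmHg), dropping to 3% at 6 mmHg. The comparable error of the between-group test is 2.5% throughout. Calling the false pattern frequent is justified only for a moderate common shift, and the documents do not say whether one is expected. The 25% is therefore a worst case and not the trial's false-positive rate. The randomised comparison, as planned and sized, is not affected.

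**What to change.** 1. Secondary objectives: remove *within-*, so that the objective is the between-group comparison.
2. Statistical analyses: make within-arm changes descriptive only, without P values, and drop the paired t and Wilcoxon tests as inferential analyses.
3. Statistical analyses: add one sentence saying that every efficacy conclusion, for SBP and for all secondary outcomes, rests on the baseline-adjusted between-group ANCOVA estimate with its 95% confidence interval. This is the essential change.

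Wording the hypotheses as barberry versus placebo would be clearer but is optional.

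No new data, participants or analyses are needed, and fewer tests are run. Recruitment had already begun according to Trial status, so changing an objective is a minor amendment. Under Protocol amendments it needs review by the principal investigator, agreement of the other investigators and a recorded justification.
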